### Ethical Considerations

Phase 1 of the study was deemed exempt by the institutional review board of the University of South Carolina (Pro00117242), and phase 2 of the study was approved by the same institutional review board. All study participants and coaches will provide written informed consent to participate in the study.

Study data will be deidentified before analyses and dissemination.

Coaches taking part in phase 1 of the study will be provided with US $100 as an incentive. Coaches taking part in phase 2 will be paid US $30 upon completion of training. In addition, coaches will be provided US $25 on delivering the intervention to their first participant and US $25 during the holiday season. Study participants (survivors) in phase 2 will be paid US $25 for completing baseline assessments and US $25 for assessments at the postintervention time point.

### Sample Size

Power calculations were based on data from our prior work with MFT [27], and data from the study by Cadmus-Bertram et al [28], who compared web-based tracking+Fitbit to pedometer alone among postmenopausal women. Comparing the effects of coach counseling [27] to web-based tracking+Fitbit [28] on changes from baseline in MVPA would yield a medium effect size, *d*=0.60. Assuming similar effect sizes and a 2-sided α=.05, we would have more than sufficient power to test intervention effects on changes in MVPA (minutes per week) at the end of intervention with 20 survivors per arm. However, given the risk of powering on pilot studies, we have conservatively inflated the sample size to 25 survivors per arm. On the basis of our prior work, we expect attrition to be ≤10% at 12 weeks, so we will recruit a total of 56 women (n=28 survivors per arm) to obtain complete data from 50 survivors.

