Aim 3a: conduct an RCT wherein 10 to 12 peer coaches will be trained to deliver webMFT to 56 survivors of breast cancer, who will be randomly assigned to receive either webMFT or MVPA tracking. We will collect quantitative and qualitative data on the acceptability and feasibility of webMFT (eg, number and duration of calls delivered and barriers experienced) and suggestions for improvement from the coaches.Aim 3b: obtain data on survivor outcomes at 12 weeks from accelerometer-measured MVPA (primary outcome) and self-reported quality of life (QOL), physical functioning, mood, and fatigue to help estimate effect sizes for a larger trial to test the impact of webMFT versus MVPA tracking on survivor effectiveness outcomes. We expect that at the postintervention time point, survivors randomized to webMFT will increase MVPA; improve QOL, physical functioning and mood; and decrease fatigue significantly more than survivors randomized to MVPA tracking.Aim 3c: assess organizational-level factors (eg, the barriers and facilitators for implementation, setting and contextual factors, resources required, and alignment of webMFT with workflow and mission) using the RE-AIM and PRISM models [18] by interviewing key multilevel stakeholders at the collaborating organizations.Aim 3d: collect detailed cost, time, and resource information to conduct cost-effectiveness analyses from the perspectives of the survivors, coaches, and cancer care organizations.Aim 3e: develop a guide on how to recruit and build collaborations with other organizations that offer peer mentor programs with which webMFT can be integrated. The long-term goal of this work is to use these data to inform a robust, large-scale pragmatic trial with several cancer care organizations to deliver webMFT to survivors of breast cancer across the country.

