### Data Analyses

#### Overview

We will examine RE-AIM dimensions (Tables 1-3) to guide us in assessing the potential for larger-scale implementation of webMFT. We will conduct descriptive analyses of reach, adoption, and implementation outcomes including acceptability and feasibility of webMFT (eg, the number and mean duration of calls, barriers, and perceived feasibility of intervention delivery as judged by coaches). According to the current recommendations [46], we will consider webMFT feasible if >75% of the scheduled calls are delivered and survivor and coach and acceptability or satisfaction exceed 80% on rating scales (ratings of “moderately” to “very satisfied/acceptable”). Feedback from coaches and survivor debrief interviews will be used to revise and update webMFT for a larger-scale implementation trial.

We will assess potential between-group differences (webMFT vs MVPA tracking) in baseline variables (eg, age and medical history) using graphical methods, nonparametric and parametric tests as appropriate (eg, Wilcoxon rank-sum test for skewed data, 2-tailed *t* tests for normally distributed continuous data, and chi-squared tests for categorical data). Any variables not balanced by randomization will be controlled for as covariates in subsequent analyses, provided they are significantly associated with the outcome under consideration (at a modest *P*<.10 level).

We will assess effectiveness by examining the effects of webMFT versus MVPA tracking on the change in survivors’ MVPA in minutes per week (accelerometer data) at 12 weeks (3 months) using a mixed effects regression model, in which we will regress MVPA at 12 weeks on baseline MVPA, randomized group, wear time, and any variables not balanced by randomization. Models will include random intercepts to adjust for repeated measures within the participant over time. We will use a similar approach to estimate the effects of group on mood, QOL, physical function, and fatigue at 12 weeks. The interest is in estimating effect sizes and CIs. Analyses will be conducted on the intent-to-treat sample with all randomized participants included. Mixed effects models use a likelihood-based approach to estimation and do not require any direct imputation of missing outcomes.

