## Results

As of September 2023, phase 1 of the study was completed, and 61 survivors were enrolled in phase 2. We expect that using newer technologies for enhanced intervention delivery, program management, and automated data collection may facilitate effective implementation by organizations with limited resources. Adapting evidence-based MFT to a customized web platform and collecting data from coaches, survivors, and organizations along with costs will provide the basis for an implementation trial to increase MVPA and its benefits among many more survivors of breast cancer.

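### The stated inputs (d=0.60, two-sided α=.05) do not give ample power: 20 per arm yields about 46% and the enlarged 25 per arm about 55% for the comparison of change scores that the Sample Size section describes

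*Protocol article*

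**What the plan says.** The Sample Size section combines the team's earlier coaching data with a cited study of web-based tracking plus Fitbit. It says that comparing the two "on changes from baseline in MVPA would yield a medium effect size, *d*=0.60". It continues: "Assuming similar effect sizes and a 2-sided α=.05", "we would have more than sufficient power to test intervention effects on changes in MVPA" (in minutes per week) "at the end of intervention with 20 survivors per arm". Because powering on pilot data is risky, it adds: "we have conservatively inflated the sample size to 25 survivors per arm". It then allows for attrition of up to 10% and plans to recruit 56 women, 28 per arm, to obtain 50 with complete data. It gives no power percentage, no SD and no baseline-to-follow-up correlation.

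Data Analyses, Overview, plans a mixed model of 12-week MVPA on baseline MVPA, group, wear time and any unbalanced variables, and states: "The interest is in estimating effect sizes and CIs". Aim 3b (Objective, Phase 2) also says the data should help estimate effect sizes for a larger trial. The same aim nevertheless expects that "survivors randomized to webMFT will increase MVPA; improve QOL, physical functioning and mood; and decrease fatigue significantly more than survivors randomized to MVPA tracking".

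**The concern.** The section gives an effect size, an α, a sidedness and a number per arm, so the adequacy claim can be checked directly. A standardised difference of 0.60 with 20 per arm is well short of the usual 80%, and moving to 25 per arm does not close the gap.

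MVPA is the primary outcome, and the results are meant to inform a large pragmatic trial. A reader who accepts that power was ample may take a non-significant MVPA result as evidence against webMFT, when the design leaves considerable room for a true effect of the assumed size to be missed. What planners of the next trial need is the precision to expect, and the section does not give it.

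**Working it through.** **Inputs.** From Sample Size: d = 0.60 on change from baseline, two-sided α = .05, n = 20 then 25 completers per arm, attrition up to 10%, 28 recruited per arm. From Data Analyses, Overview: adjustment for baseline MVPA. The correlation ρ between baseline and 12-week MVPA is not given, so a range is shown.

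**Step 1: the plan's attrition figure.** 25 / 0.9 = 27.8, rounded up to 28 per arm, or 56 in total; 56 × 0.9 = 50.4 completers. This step reproduces and is not in question.

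**Step 2: unadjusted comparison of change scores.** Two-sample t test with noncentrality d·√(n/2) and 2n − 2 degrees of freedom.

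| Completers per arm | Noncentrality | Power |
|---|---|---|
| 20 | 0.60 × √10 = 1.90 | 45.6% |
| 25 | 0.60 × √12.5 = 2.12 | 54.7% |
| 28 (no attrition) | 0.60 × √14 = 2.24 | 59.7% |
| 45 | 0.60 × √22.5 = 2.85 | 80.4% |

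Forty-four per arm gives 79.5%, so 45 is the smallest number that reaches 80%. At 10% attrition that means recruiting 45 / 0.9 = 50 per arm. The normal approximation agrees: 47.5% at 20, 56.4% at 25, and 44 per arm for 80%. Working back, the d detectable with 80% power is 0.91 at 20 per arm and 0.81 at 25 per arm.

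**Step 3: baseline-adjusted model, d on the change-score SD.** With equal baseline and follow-up variance σ², the change-score SD is σ√(2(1 − ρ)) and the adjusted residual SD is σ√(1 − ρ²). The effective d is therefore 0.60 × √(2/(1 + ρ)).

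| ρ | Effective d | Power, 20 per arm | Power, 25 per arm |
|---|---|---|---|
| 0 | 0.85 | 74.4% | 83.6% |
| 0.1 | 0.81 | 70.3% | 80.0% |
| 0.3 | 0.74 | 63.1% | 73.2% |
| 0.5 | 0.69 | 57.0% | 67.0% |
| 0.7 | 0.65 | 51.8% | 61.6% |

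The 20 per arm that the section calls ample stays below 75% throughout. The 25 per arm reaches 80% only at ρ of about 0.1 or lower.

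**Step 4: baseline-adjusted model, d on the follow-up SD.** The effective d is now 0.60 / √(1 − ρ²). For 80% power it must equal 0.91 (20 per arm) or 0.81 (25 per arm), so ρ = √(1 − (0.60/0.909)²) = 0.75 or √(1 − (0.60/0.809)²) = 0.67.

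**Step 5: other routes.** One-sided testing at .05 gives 58.7% (20 per arm) and 67.2% (25 per arm), and the section specifies two-sided. A within-arm paired test gives 72.1% and 82.1%, but it is not the between-arm comparison.

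**Step 6: precision.** At d = 0.60 and 25 per arm, SE(d) = √(2/25 + 0.60²/(4 × 25)) = √0.0836 = 0.289. The 95% half-width is 1.96 × 0.289 = 0.57, so an observed d of 0.60 would carry an interval of about 0.03 to 1.17, unadjusted.

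**The case against.** The strongest reply is that the planned analysis is not the unadjusted test. This stands in part. A reader might infer that 55% is the power of the planned model, or that the trial would miss a true d of 0.60 nearly half the time. The document does not support either inference. With adjustment and d on the change-score SD, 25 per arm gives about 62% to 84% for ρ from 0.7 to 0, a miss rate of 16% to 38%. That still leaves the claim made for 20 per arm without support.

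Second, the section does not name the SD behind d, and d comes from contrasting two separate studies. On the follow-up SD with a high enough correlation, 80% is attainable. This cannot be excluded, but the section speaks of changes from baseline, which points to the change-score SD, and it states no correlation.

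Third, the declared interest is estimation, and the wording in Aim 3b is an expectation, not a decision rule. That lessens the consequence and would justify 25 per arm without any power claim. It does not make the power claim true.

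A reader might also infer a multiplicity problem from the five outcomes in Aim 3b, or an overrun from the statement that "61 survivors were enrolled in phase 2". Neither follows. MVPA is the single primary outcome and no success claim rests on any one of five tests. Consent and baseline screening precede randomization, so enrolled need not mean randomized. Even 30 completers per arm would give only about 63% unadjusted.

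**Conclusion.** The adequacy claim is wrong as written. On the stated inputs, power is about 46% at 20 per arm and 55% at 25 per arm for the comparison of change scores that the section describes, against 45 completers per arm for 80%. Baseline adjustment raises this to about 67% at 25 per arm with ρ = 0.5 but does not bring 20 per arm to 80%. The adjusted figures assume d on the change-score SD, equal baseline and follow-up variances, and no further gain from wear time or other covariates. Because the sample is selected for low baseline activity, the equal-variance assumption is uncertain; a moderately smaller baseline variance would lower these powers. The one reading that reaches 80% at 20 per arm needs a different SD and a correlation that the article does not state.

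The fault lies in the stated justification, not in the attrition arithmetic, the analysis model or the conduct of the trial. The estimation purpose is already in the text and remains sound at this size.

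**What to change.** In Sample Size, delete the claim that power is more than adequate and state what the design provides:

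- 25 completers per arm give about 55% power for d = 0.60 in an unadjusted comparison of change scores.
- With baseline adjustment this is about 62% to 73% for ρ from 0.7 to 0.3, with d on the change-score SD and equal variances.
- Unadjusted power is 80% for d of about 0.81.
- The expected 95% CI half-width is about 0.57 SD, unadjusted.

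If a different SD or a specific correlation was assumed, state it with the power that results.

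Present the MVPA comparison as estimation with 95% CIs, in line with Data Analyses, and reword Aim 3b so that it no longer predicts statistically significant differences.

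The cost is wording and a less favourable stated power. No extra participants are needed, and the analysis does not change.

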### Study Implementation

#### Survivor Enrollment

Each survivor will be asked to obtain medical consent from her oncologist to enroll. Providers will be allowed to exclude patients if the MVPA goal would be unsafe for the patient. Intervention delivery will begin after informed consent, medical consent, and baseline data are obtained.

#### Random Assignment

Survivors will be randomly assigned to a group after informed consent and baseline data are obtained. Consistent with prior work, the sample will be stratified for 2 variables that may affect MVPA outcomes (age: <60 years or >60 years; and treatment: received or not received chemotherapy). The randomization scheme will be generated using the R (the R Foundation for Statistical Computing), based on a permuted block randomized procedure with small, random-size blocks so that equal numbers of survivors are randomized to webMFT or MVPA tracking by age and treatment. The project director will contact the survivor and disclose the group assignment from a sealed envelope.

#### Matching

The coach-survivor matching criteria for survivors randomized to webMFT will include mandatory and preference-driven criteria. The mandatory criterion is overlapping times on their respective schedules. The preference-driven criteria include age (+10 years or −10 years), type of cancer treatment (eg, radiation), race, and ethnicity. If >1 matching coach exists, preference-driven criteria will be used to identify an appropriate coach. Following matching, the first call between a coach and a survivor will be scheduled. The coach will receive an alert (email and text, depending on preference) that a new survivor has been added to the queue.

#### The webMFT Group

Survivors randomized to webMFT will receive the evidence-based MFT program for MVPA promotion [29] that consists of MVPA counseling matched to patients’ motivational readiness and self-monitoring of MVPA (Fitbit activity tracker).

#### Exercise Counseling

Coaches will be asked to contact survivors using the web platform and make 12 calls (1 call per week over 12 weeks). Each call will take approximately 15 to 20 minutes. The purpose of the calls is to build a supportive relationship with the survivor, assess motivational readiness, review MVPA participation (participant Fitbit data viewed on the web platform), identify any health concerns, assist the survivor to identify relevant barriers to MVPA, and help her to problem solve such barriers and set MVPA goals. In addition, the coach will provide feedback and reinforce and encourage efforts to start being active and stay active. The counseling will be matched to the survivor’s motivational readiness assessed at the start of each call. For example, women in the precontemplation stage will be given information to increase their awareness of the benefits of MVPA after cancer treatments (eg, improved physical functioning). The goal, as in prior work, will be to gradually increase the amount of moderate intensity aerobic exercise that is performed to the current national recommendations of at least 150 minutes of MVPA per week [7]. Coaches will be trained not to provide medical advice but to encourage patients to contact their oncologist for medical care and health issues. If patients report symptoms such as chest pain or difficulty breathing, participation will be temporarily halted, and they will be referred to their oncologist.

#### Self-Monitoring of MVPA

Survivors will be asked to self-monitor MVPA participation (frequency, duration, steps, and heart rate during MVPA) by wearing the Fitbit activity tracker each day. These data will be automatically uploaded to the webMFT platform via the Fitbit Application Programming Interface integrated into the Mentor1to1 platform. Participants will be encouraged to sync their Fitbit daily via Bluetooth. Automated reminders to sync the tracker will be sent from the web platform. Coaches will be able to email or text the participant their Fitbit data (chiefly, active minutes) as shown on the web platform. Coaches will review their survivor’s weekly MVPA during calls and enter these data into the web platform.

#### MVPA Tracking Group

These survivors will be asked to self-monitor MVPA participation (frequency, duration, and heart rate during MVPA) by wearing the Fitbit device each day over 12 weeks (3 months). They will be able to see the feedback that the tracker provides on the app dashboard (eg, daily MVPA minutes) and can access other Fitbit features. They will receive weekly text reminders from the research staff members to sync the tracker. The research staff members will review Fitbit data through the Fitbit dashboard to ensure that the device is worn and routinely synced. This group will be provided with the same 12 tip sheets as those provided to webMFT group and the procedures to follow in the event of any injury. This comparison arm thus constitutes a real-world, low-cost intervention.

#### Training Coaches

Before beginning training, coaches will receive a training manual. On the basis of prior work, we will develop recorded training modules that provide information on the benefits of exercise for survivors of cancer; TTM and SCT; training on counseling techniques (eg, empathy and reflective listening); working with human participants and HIPAA regulations; and emergency protocols. In addition, trainers will offer 1 live internet-based group training session during which coaches will practice role plays and receive feedback through videoconferencing. Coaches will complete a second live internet-based individual training session to ensure that they can deliver the intervention while using the platform, using screen sharing capabilities between the coach and research staff. Coaches will be trained to query patients at each call about health symptoms and notify the research staff immediately if survivors endorse any symptoms that are potentially indicative of a serious problem. In these cases, study participation will be temporarily halted until the medical issue has been resolved. Coaches will receive a supervision call every other week from research staff members through the web platform.

### Measures

#### Overview

In phase 2, we will collect RE-AIM outcome measures from survivors, coaches, and organizational staff members as well as key contextual and organizational factors that influence RE-AIM outcomes using PRISM (Tables 1-3). Quantitative and qualitative data will be collected. Perspectives from the survivors, coaches, and organizational staff members will be obtained through semistructured interviews. Interview guides will be developed based on the RE-AIM outcome dimensions and PRISM domains of contextual influence. The RE-AIM outcome dimensions assessed include Effectiveness, as well as the implementation outcomes of Reach, Adoption, Implementation, and Maintenance. The PRISM domains include: (1) perspective of the intervention at the level of the survivor, coach and organization; (2) organizational characteristics; (3) external environment; and (4) implementation and sustainability infrastructure [17,18].

**Table 1 table1:** Quantitative data collection for effectiveness outcomes.

Effectiveness outcome	Measure	Participant level	Time point	
		Survivors	Baseline	12 weeks
MVPA^a^	Accelerometer (Actigraph GT3X) worn over 7-d period	✓	✓	✓
QOL^b^	36-item Short Form Health Survey	✓	✓	✓
Physical functioning	FACT-B^c^	✓	✓	✓
Fatigue	FACT-F^d^	✓	✓	✓
Mood	POMS^e^	✓	✓	✓
Stages of change	Stage of Readiness for Exercise	✓	✓	✓
Self-efficacy for exercise	Exercise Self-Efficacy Scale	✓	✓	✓

^a^MVPA: moderate to vigorous physical activity.

^b^QOL: quality of life.

^c^FACT-B: Functional Assessment of Cancer Therapy Scale-Breast.

^d^FACT-F: Functional Assessment of Cancer Therapy Scale-Fatigue.

^e^POMS: Profile of Mood States.

**Table 2 table2:** Quantitative data collection for reach, adoption, and implementation outcomes.

RE-AIM^a^ dimension and PRISM^b^ domain outcome			Measure	Participant level			Time point	
				Survivor	Coach	Organization	Baseline	12 weeks
**Reach**								
	Total potential survivors in participating organizations		Count	✓			✓	
	Number of survivors eligible to participate (meet study eligibility criteria)		Count, % of total	✓			✓	
	Number of survivors excluded by the investigator due to not meeting eligibility criteria for study		Count, % of total	✓			✓	
	Reasons survivors excluded by the investigator		Descriptive data tracked by the study team	✓			✓	
	Number of eligible survivors who agree to enroll		Count, % of eligible	✓			✓	
	Number of eligible survivors who decline		Count, % of eligible	✓			✓	
	Reasons eligible survivors decline		Tracked by study team	✓			✓	
**Adoption**								
	Total number of potential settings		Count			✓	✓	
	Number of settings eligible (based on organizational readiness criteria)		Count, % of total			✓	✓	
	Number of settings excluded by investigator (based on organizational readiness criteria)		Count, % of total			✓	✓	
	Reasons settings excluded by the investigator		Settings score <4 on ORIC^c^ questions or <4 on single-item organizational readiness survey or informed study team not ready or PI^d^ discretion			✓	✓	
	Number of eligible settings that agree to participate in MFT^e^		Count, % of eligible			✓	✓	
	Number of eligible settings that decline to participate in MFT		Count, % of eligible			✓	✓	
	Reasons eligible settings choose to agree to participate or decline to participate in MFT		Open-ended item at the end of ORIC survey			✓	✓	
	Number of eligible settings not contacted or other		Count, % of eligible			✓	✓	
	Setting: characteristics of adopters vs nonadopters		Number of employees, location, etc			✓	✓	
	Within each site, number of coaches who agree to participate in MFT		Count, % within a participating setting		✓		✓	
	Within each site, number of coaches who decline to participate in MFT		Count, % within a participating setting		✓		✓	
	Reasons coaches choose to decline to participate in MFT		Tracked by the study team		✓		✓	
	Coaches: characteristics of adopters vs nonadopters		Age, sex, race, ethnicity, and baseline activity levels		✓		✓	
